**6. SUBJECT SELECTION**

**6.1. INCLUSION CRITERIA**

1. Signed informed consent

2. Age 18 or older

3. Confirmed histological diagnosis of lymphocytic enteropathy (LE)*

5. Coeliac-positive genetic study (HLA-DQ2 and/or HLA-DQ8)

6. Negative coeliac serology

7. Complete clinical and histological response to gluten-free diet

8. Initial clinical signs with or without extra-intestinal manifestations

*Lymphocytic enteropathy is defined as an intraepithelial lymphocyte count greater than 25 per 100 epithelial cells, using histochemical techniques with anti-CD3 monoclonal antibodies for the count.

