**8. DEVELOPMENT OF TRIAL AND ASSESSMENT OF RESPONSE**

**8.1. PRINCIPAL AND SECONDARY ASSESSMENT VARIABLES**

**Efficacy criteria**

- Primary efficacy evaluation variable: Reappearance of clinical digestive signs (24 weeks)
- In addition, secondary efficacy variables will be evaluated:
  - Clinical signs at 4 weeks
  - Clinical signs at 12 weeks
  - Flow cytometry to measure percentage of lymphocytes CD3+ gamma-delta+ and CD3- in intestinal mucus membrane
  - Assessment of IgA tissue anti-transglutaminase antibodies in the intestinal mucus membrane
  - IgA tissue anti-transglutaminase antibodies in serum and anti-endomysium antibodies
  - Quality of life according to the GIQLI questionnaire.
  - Histological changes on biopsy in the distal duodenum

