**8.3. DESCRIPTION OF METHODS USED TO ASSESS RESPONSE**

Clinical response will be measured with analogue visual scales ranging from 0 to 100, administered at baseline and at each visit up to 6 months, for symptoms of abdominal pain, abdominal swelling, diarrhea, and flatulence (total score 0 to 400 points) (Appendix 6).

Patient quality of life will be evaluated in the first visit and the last (at 6 months, or at early withdrawal) using the GIQLI questionnaire (Gastrointestinal Quality of Life Index), which has been shown to yield valid, reliable scores for the detection of significant clinical changes in the lives of patients regarding their health (Eypasch E et al. Gastrointestinal Quality of Life Index: development, validation and application of a new instrument. Br J Surg 1995; 82:216-22; Quintana JM et al. Translation and validation of the Gastrointestinal Quality of Life Index (GIQLI). Rev Esp Enferm Dig 2001; 93:693-706) (See Appendix 3).

At the first visit and the last (or at early withdrawal from the study) a distal duodenal biopsy will be drawn for histological study, and evaluation of tTG deposits and lymphocytic sub-populations (using flow cytometry) will be made.

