**13. STATISTICAL ANALYSIS**

The calculation for the sample size is based on the main variable of efficacy—that is, the rate of recidivism at 6 months. On the basis of results of previous studies it was determined that the rate of recidivism with the reintroduction of gluten would be 80%, and with placebo 20%. Assuming a 10% patient drop-out rate, an alpha value of 5%, and statistical power (beta) of 80%, for a bilateral test it was calculated that 10 patients would be needed for each patient group (bearing in mind that analyzing the results would require a Chi-square test with Yates correction). The total number, then, is 20 patients.

Excluded from this analysis are those subjects presenting significant departures from the protocol.

All of the evaluations of the primary and secondary variables, both of efficacy and of safety, are understood in the exploratory sense (alpha=0.05, bilateral).

The Chi-square test with Yates correction will be used for independent groups and the Fisher exact test for qualitative variables. For intergroup comparison of the quantitative variables, the Student-t test will be used for parametric variables, and the Mann-Whitney U-test for non-parametric variables.

The finding of values for differences of p less than 0.05 will be considered significant. The rates for clinical remission between treatment groups will be expressed proportionally with the corresponding bilateral interval of confidence of 95%, as an estimation of therapeutic effect.

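### Section 13 names only unadjusted tests for quantitative outcomes and does not say whether follow-up values or changes are compared; ANCOVA on the baselines already collected would usually be more precise.

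*Protocol*

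**What the plan says.** Protocol section 13 sets one rule for all quantitative outcomes: "For intergroup comparison of the quantitative variables, the Student-t test will be used for parametric variables, and the Mann-Whitney U-test for non-parametric variables". Neither section 13 nor any other part of the protocol mentions a covariate, baseline adjustment or change from baseline. The rule names the tests but not the quantity to be tested.

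Section 8.3 has the same outcomes measured more than once:
- The symptom score (four visual analogue scales, total 0 to 400) is "administered at baseline and at each visit up to 6 months".
- For the GIQLI, "Patient quality of life will be evaluated in the first visit and the last".
- For tissue, "At the first visit and the last (or at early withdrawal from the study) a distal duodenal biopsy will be drawn for histological study", and at the same times "evaluation of tTG deposits and lymphocytic sub-populations (using flow cytometry) will be made".

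Sections 6.3 and 13 set 10 patients per arm. Section 13 calls all evaluations, primary and secondary, exploratory at a two-sided 5% level. The sample size there rests on a recurrence rate, so the primary endpoint as sized is binary and this rule does not reach it.

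**The concern.** In a trial of 20 patients, chance differences between the arms at baseline can be large. Where an outcome's baseline predicts its follow-up value, part of that difference carries over into the follow-up comparison and adds noise. Using the baseline as a covariate removes this noise, and here the baseline values, including an invasive biopsy, are collected anyway.

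The wording leaves a second gap. A t-test on follow-up values and a t-test on changes both fit section 13, and their precision can differ greatly. If the choice is not written down, it can be made after the data are seen.

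At stake are the quantitative secondary outcomes. Section 4.1 looks partly to immunological measurements in the intestinal mucosa to separate coeliac disease from non-coeliac gluten sensitivity, so the flow-cytometry percentages are of real interest.

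**Working it through.** The protocol gives no power figure for a quantitative outcome, so there is none to reproduce. The question is how the two readings of section 13 compare with ANCOVA.

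**Inputs from the protocol.** 10 per arm (n = 10, N = 20), 1:1 allocation, two-sided 5% (sections 5.1, 6.3 and 13).

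**Assumptions, not in the protocol.** True effect 1 SD; equal SD at baseline and follow-up; normal data; correlation r between baseline and follow-up, shown at 0, 0.3, 0.5 and 0.7.

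**Chance imbalance.** The standard error of the baseline difference is √(2/10) = 0.45 SD. It carries into the follow-up difference in proportion to r: about 0.22 SD at r = 0.5 (0.447 × 0.5) and 0.31 SD at r = 0.7 (0.447 × 0.7).

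**Variance of the treatment difference, relative to the follow-up t-test:**
- Follow-up t-test: 1, with 18 degrees of freedom.
- Change-score t-test: 2(1 − r), with 18 degrees of freedom.
- ANCOVA: (1 − r²)(N − 3)/(N − 4) = (1 − r²) × 17/16, with 17 degrees of freedom.

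**Power.** From the noncentral t distribution with noncentrality 1/√(0.2 × relative variance). For the follow-up t-test this is 1/√0.2 = 2.236, giving 56% power at every r.

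| r | Change: relative variance | Change: power | ANCOVA: relative variance | ANCOVA: power | ANCOVA CI width ÷ follow-up t-test CI width |
|---|---|---|---|---|---|
| 0 | 2.00 | 32% | 1.06 | 53% | 1.035 |
| 0.3 | 1.40 | 43% | 0.97 | 57% | 0.987 |
| 0.5 | 1.00 | 56% | 0.80 | 66% | 0.896 |
| 0.7 | 0.60 | 78% | 0.54 | 82% | 0.739 |

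**Break-even against the follow-up t-test.** On variance alone, (1 − r²) × 17/16 = 1 gives r = √(1/17) = 0.24. Allowing also for the lost degree of freedom, power and interval width break even at about r = 0.26.

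**Simulation check.** 40,000 simulated trials per r, 10 per arm, gave ANCOVA/follow-up variance ratios of 1.06, 0.96, 0.79 and 0.54, in line with the formula.

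**The case against.** A reader might infer that the plan throws the baseline values away. The text does not say so: a t-test or Mann-Whitney test on changes fits section 13 and uses the baseline. Against that reading the advantage of ANCOVA is smaller: variance 0.80 against 1.00 at r = 0.5 (20% less) and 0.54 against 0.60 at r = 0.7 (10% less). This stands. It does not rescue the plan, because ANCOVA is ahead of the change score at each of the four correlations shown, and below r = 0.5 the change score does worse than ignoring baseline.

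A reader might also infer that the comparison is biased. It is not. Under randomization the unadjusted test is valid and its confidence interval already allows for chance imbalance. The loss is one of efficiency.

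The gain depends on r, and r may be low. Section 6.1 requires "Complete clinical and histological response to gluten-free diet", so symptom scores and histology start from a compressed range. The GIQLI is only partly free of this: 19 of its 36 items in Appendix 3 (items 1-9 and 27-36) are labelled as symptoms. Relapse can lower r further. As an illustration, take the 80% and 20% recurrence rates of section 13 and assume relapse shifts a score by 3 SD. The within-arm variance rises from 1 to 1 + 0.8 × 0.2 × 9 = 2.44, and r = 0.5 falls to 0.5/√2.44 = 0.32, where ANCOVA reduces variance by only about 5%. This stands as a limit on the size of the gain. Flow cytometry is the outcome least obviously tied to the remission criterion.

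Finally, covariates are often left to a statistical analysis plan, and one may exist. But section 13 does not leave the method open: it names the tests that will be used. An adjusted analysis in a later plan would depart from that wording, so the protocol text is worth changing.

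**Conclusion.** The point holds as one of efficiency and incomplete specification. Section 13 names valid but unadjusted tests and leaves open whether follow-up values or changes are analysed, although baselines of the same outcomes are collected.

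Against the follow-up t-test, ANCOVA gains about 10 points of power at r = 0.5 (66% against 56%) and about 25 at r = 0.7 (82% against 56%). It gains almost nothing at r = 0.3 and loses about 3 points at r = 0. These figures rest on an assumed 1 SD effect, normal data and correlations that the protocol does not give. The gain could be small for symptom score and histology.

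The consequence is limited to secondary outcomes that the protocol itself calls exploratory. The documents give no ground for extending it to the primary recurrence comparison or to the sample size.

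**What to change.** In section 13, replace the rule for quantitative outcomes measured at both times. Analyse each by ANCOVA of the follow-up value on treatment, with the outcome's own baseline value as covariate, and report the adjusted difference with its 95% confidence interval. This also settles whether follow-up or change is compared. Name in advance which outcomes will use a rank-based version, rather than deciding from the residuals.

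The change needs no new data, visits or patients. It uses one degree of freedom; if baseline proves uninformative, that costs about 3 points of power (53% against 56% in the setting above) and a confidence interval about 3.5% wider.

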**APPENDIX 1**

**Gluten 10 g single-dose product characteristics**

**Xalabarder Pharmacy ([name])**

1. **PRODUCT DESCRIPTION**

Gluten 10g single-dose.

1. **COMPOSITION**

This product consists of 10g of gluten per unit.

1. **PRESENTATION**

Single-dose sachets with 10g of product.

Boxes of 60 sachets.

6 boxes for each treatment.

1. **RAW MATERIAL**

Raw material purchased from Fagron Ibèrica.

The certificate of analysis lists the following assays and results:

|  | **GLUTEN** | |
| --- | --- | --- |
| **ASSAYS** | | **RESULTS** |
| **Loss through desiccation** | | 7.8% |
| **pH** | | <5 |
| **Total ash** | | 0.9% |
| **Proteins** | | 82 |
| **Fiber** | | 0,5 |
| **Fatty material** | | 1.3 |
| **Carbohydrates** | | 9 |
|  | | **SPECIFICATION COMPLEX** |

1. **PACKAGED MATERIAL**

Thermally sealed aluminum and cellulose Surling-type blister pack.

Sachets are marked with production reference number and expiration date. As per request they do not indicate composition of contents.

Boxes carry the following label:

1. **EXPIRATION**

Product expiration date: 29/5/2012

1. **PREPARATION**

Date: 29/5/2009

Reference: 820055963

Approval: Prepared using the standards for preparation of powders for single-dose oral use. Passed quality control and marked as ‘approved’.

1. **INDICATION**

The product was requested by the Mútua de Terrassa Pharmacy Service for clinical trial EL-DSG/01/01: gluten/maltodextrin.

1. **SIGNATURE**

| **Technical Director** | **Quality Guarantee Unit** |
| --- | --- |
| [name] | [name] |

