**3.8. EXPECTED DURATION OF TRIAL**

Maximum recruitment period: 30 months

Maximum treatment period: 6 months

Maximum total duration: 36 months

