**5.2. MASKING METHODS**

In order to mask the gluten and placebo supplements they will be given the same organoleptic characteristics. They will be administered in non-transparent sachets filled with dry powder, with no difference in appearance between the consecutively numbered product packaging for the two treatment groups.

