**7.2. MEANS TO ASSESS COMPLIANCE**

Assessment of compliance will be made by counting the number of sachets returned at each visit and by reviewing what is recorded in the patient diary.

A standard gluten-free diet will be prescribed in writing. A dietician or expert nutritionist will see each patient each month to evaluate how closely the diet is being followed (Appendices 4 and 5).

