**APPENDIX 2**

**Maltodextrin 10 g single-dose product characteristics**

**Xalabarder Pharmacy ([name])**

1. **PRODUCT DESCRIPTION**

Maltodextrin 10g single-dose.

1. **COMPOSITION**

This product consists of 10g of maltodextrin per unit.

1. **PRESENTATION**

Single-dose sachets with 10g of product.

Boxes of 60 sachets.

6 boxes for each treatment.

1. **RAW MATERIAL**

Raw material purchased from Fagron Ibèrica.

The certificate of analysis lists the following assays and results:

|  | **MALTODEXTRIN** | |
| --- | --- | --- |
| **ASSAYS** | | RESULTS |
| **Identification** | | Passed |
| **Loss through desiccation** | | 4.74% |
| **Heavy metals** | | <10ppm |
| **Sulphur ash** | | <0.5% |
| **pH** | | 6.02 |
| **Sulphur dioxide** | | <5ppm |
| **Total airborne material** | | <10ufc/g |
| **Fungi and yeast** | | <10ufc/g |
| **E. Coli** | | Passed |
| **Salmonella** | | Passed |
| **Dextrose** | | Passed |
|  | | **SPECIFICATION COMPLEX** |

1. **PACKAGED MATERIAL**

Thermally sealed aluminum and cellulose Surling-type blister pack.

Sachets are marked with production reference number and expiration date. As per request they do not indicate composition of contents.

Boxes carry the following label:

1. **EXPIRATION**

Product expiration date: 29/5/2012

1. **PREPARATION**

Date: 29/5/2009

Reference: 820055964

Approval: Prepared using the standards for preparation of powders for single-dose oral use. Passed quality control and marked as ‘approved’.

1. **INDICATION**

The product was requested by the Mútua de Terrassa Pharmacy Service for clinical trial EL-DSG/01/01: gluten/maltodextrin.

1. **SIGNATURE**

| **Technical Director** | **Quality Guarantee Unit** |
| --- | --- |
| [name] | [name] |

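### Sachets appear to carry a production reference that differs between gluten and placebo and is decoded in the appendices; this conflicts with section 5.2 and leaves the blind open to being broken

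*Protocol*

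**What the plan says.** Section 5.2 of the protocol promises opaque sachets of dry powder, "with no difference in appearance between the consecutively numbered product packaging for the two treatment groups". Sections 5.1 and 7.4 add that the medication is coded and numbered in sequence, is dispensed through the hospital pharmacy, and that the evaluator stays blind to the randomization key.

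Section 7 points to Appendix 1 for the gluten supplement and Appendix 2 for the placebo. On packaging, Appendix 1 states: "Sachets are marked with production reference number and expiration date. As per request they do not indicate composition of contents". Appendix 2 repeats it for maltodextrin: "Sachets are marked with production reference number and expiration date". Under the preparation heading, Appendix 1 (gluten) gives "Reference: 820055963" and Appendix 2 (maltodextrin) gives "Reference: 820055964".

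Section 7.2 assesses compliance by "counting the number of sachets returned at each visit". Section 9.2.2 lets the sponsor unmask isolated cases for safety.

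Both appendices also state "Product expiration date: 29/5/2012" and say that the product was requested for a trial coded EL-DSG/01/01. This trial is EL-DSG/07/2011, and section 3.8 gives "Maximum total duration: 36 months".

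**The concern.** A number that is unique to a patient says nothing about that patient's arm without the randomization list. A number shared by all sachets of one product does, and here the protocol itself prints which number belongs to which product. The packer was asked to leave the composition off the sachet but was apparently left to print a reference that stands in for it.

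The outcome makes this matter. The primary variable in section 8.1 is the return of digestive symptoms, and section 8.3 measures clinical response with visual analogue scales that patients mark themselves. Participants have already responded completely to a gluten-free diet (section 6.1), so many will expect gluten to bring symptoms back. If knowledge of the arm reached staff, it could colour how symptoms are elicited, how a relapse is judged or when a patient is withdrawn. If it reached patients, it could colour the scores directly.

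**Working it through.** No sample-size or power formula applies. The check sets the passages side by side.

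1. **Is there a mark on the dose unit?** Yes. Both appendices say that the sachets are marked with a production reference and an expiry date.

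2. **Does the mark differ by arm?** The listed references are 820055963 (gluten) and 820055964 (maltodextrin). 820055964 − 820055963 = 1, so they are not equal. The expiry date is 29/5/2012 for both and does not identify the arm. That the printed production reference is the reference listed under preparation is an inference. It is a strong one, since each appendix lists only one reference.

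3. **Are these the products of this trial?** Section 7 cites the two appendices as such.

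4. **Is the mark neutralised elsewhere?** Sections 5.1, 5.2 and 7.4 add consecutive numbering. None says that the production reference is removed, covered or made common to both products.

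5. **Who is exposed to it?**
   - A patient who completes treatment uses 24 weeks × 7 days × 2 sachets = 336 sachets. The described supply of 6 boxes × 60 = 360 sachets fits one such course.
   - Returned sachets are counted at each visit, so whoever counts them can see the mark. Section 7.2 does not say who that is.
   - Section 7.4 blinds the evaluator to the randomization key, but the sachet mark would bypass the key.
   - If each arm is supplied from one batch, the 10 patients in an arm share one number. One unmasked case would then classify all 20 patients for anyone who sees their sachets, even without the appendices.

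6. **The batch, as a separate matter.** A 24-week course is 168 days, and 29/5/2012 minus 168 days is 13/12/2011. Only patients who start by that date could finish on the described batch. The protocol cites a paper dated 11 January 2011, so its text cannot be older than that. From 11/1/2011 to 29/5/2012 is 354 + 150 = 504 days, or 504 / 30.44 ≈ 16.6 months, against up to 36. If the trial began around 1 July 2011 (an assumption read from its code), the figure is 333 / 30.44 ≈ 10.9 months.

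**The case against.** The strongest reply is that nothing here shows a broken blind. A reader might infer from the two numbers that it is broken, but the documents do not support that. The pharmacy's consecutive numbering may replace or cover the manufacturer's mark; the text does not say either way. The identity of the printed number with the listed reference is inferred. The listed batch was requested under another trial code and expires early, so the sachets dispensed later may bear numbers that the appendices do not decode. All of this stands. It limits the point to a conflict in the text and an open route to unmasking. It does not remove the conflict, because section 7 still adopts these appendices. Under the same marking specification, two separately prepared products could again carry two references unless a common code is used.

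It can also be said that patients have no route to their allocation. They receive an information sheet and a consent form, are not said to receive Appendices 1 and 2, and see one nine-digit number with nothing to compare it with. That stands too. The exposure is mainly among staff and others who see several patients' sachets.

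A reader might also infer that a positive result could be expectation alone, and try to put a false-positive rate on it. With 10 per arm and a true relapse rate of 20% in both, the exact rejection probability of the Yates-corrected test is 0.8%. If knowing the arm raised reported relapse on gluten to 40%, 50% or 60%, it would be 5.8%, 13.2% or 25.3%. These figures are arithmetically right, but nothing in the documents supports the 40% to 60% rates. The placebo rate is held at 20% although the same expectation could lower it, and the calculation presumes that patients know their arm. It does not measure the effect of a sachet number. Biopsy, flow cytometry and tissue antibody deposits are also collected and are not self-reported. The summary in section 1 even lists histological recurrence with symptoms as primary, whereas section 8.1 lists symptoms alone.

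**Conclusion.** The point holds as a contradiction in the masking plan. As written, sachets carry a product-specific reference that the appendices pair with gluten or placebo, while section 5.2 says that the packaging does not differ between groups. The blind is therefore open to being broken by someone with the protocol and a sachet in hand, or by someone who sees several patients' sachets after one case is known. The documents do not show that it was or will be broken.

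This rests on two assumptions: that the printed number is the listed reference, and that pharmacy numbering does not hide it. Inspecting one sachet of each product as dispensed would settle both. The resulting bias cannot be sized from the documents. The point deserves action because symptoms are primary under either statement of the endpoint, and lost blinding cannot be restored by analysis.

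The batch's expiry and trial code are a separate supply and documentation matter and add no weight to the masking point. The box label is not reproduced in the copy at hand, so nothing is concluded about it.

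**What to change.** - Specify in sections 5.2 and 7.4 that patient packs, including each sachet, show the participant or kit number only, or else a code common to both products. Any manufacturer's reference should be left off or over-labelled before dispensing.
- Keep the link from batch to arm in the pharmacy, out of reach of blinded staff.
- Remove the two reference numbers from the copies of Appendices 1 and 2 that blinded staff hold.
- State in section 7.2 who counts returned sachets. If the mark cannot be covered, this should be pharmacy staff outside the assessment.
- Separately, reconcile the described batch (requested for EL-DSG/01/01, expiry 29/5/2012) with this trial's code and the duration in section 3.8, and apply the same labelling rule to any replacement batch.

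The cost is a label specification, an edited appendix and a pharmacy log. The one small downside is that batch traceability moves from the sachet to that log. The expiry date needs no change for masking, as it is already the same on both products.
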